### Study Objectives and End Points

#### Objectives

The objectives of the study are (1) to determine the safety of TANCoV-1.3.20 at a dose of 100 µL with or without a booster and 200 µL without a booster delivered nasally, (2) to assess the tolerability of TANCoV-1.3.20 at a dose of 100 µL with or without a booster and 200 µL without a booster delivered nasally, (3) to determine the immunogenicity of TANCoV-1.3.20 at a dose of 100 µL with or without a booster and 200 µL without a booster delivered nasally, (4) to compare the immunogenicity of TANCoV-1.3.20 at a dose of 100 µL with or without a booster and 200 µL without a booster delivered nasally, (5) to explore the factors influencing the willingness and acceptability of participants to participate in local COVID-19 vaccine trials, and (6) to assess the perceptions of study participants and their social environment toward the TANCoV-1.3.20 vaccine.

#### Primary End Points

Safety will be assessed using clinical and laboratory parameters. We will grade clinical, hematological, and biochemical tests, as well as evaluate the frequency, severity, and duration of adverse events (AEs). AEs will be graded according to the Division of AIDS toxicity grading table, version 2.1, July 2017.

##### Safety End Points: Incidence of AEs (Safety and Tolerability)

The safety end points are (1) the proportion of participants with local and systemic solicited AEs from days 1 to 7 after each intraperitoneal (IP) administration; (2) the proportion of participants with grade 2 or higher unsolicited AEs, including safety laboratory (biochemical and hematological) parameters, from the day of each IP administration through 28 days after IP administration; and (3) the proportion of participants with serious AEs (SAEs) throughout the study period.

##### Secondary End Points: Immunogenicity End Points

The secondary end points are (1) the proportion of participants with a specific TANCoV-1.3.20 humoral response, (2) the magnitude of the specific cellular response to TANCoV-1.3.20, (3) the proportion of participants with serum-neutralizing antibody responses to TANCoV-1.3.20, and (4) the characteristics of the humoral response produced by the TANCoV-1.3.20 vaccine.

##### Capacity Building and Social Aspects of the Trial End Points

The capacity building and social aspects of the trial end points are (1) the number of personnel who acquired international critical skills, knowledge, and strengthened infrastructure for conducting a clinical trial; and (2) the perception, willingness, and acceptability of the TANCoV-1.3.20 vaccine trial among study participants and their social environment.

### Sample Size Estimation

The sample size for this noninferiority clinical trial was calculated to compare the proportion of seroconversion on day 28 between participants receiving the investigational vaccine TANCoV-1.3.20 and those receiving the standard Sinopharm COVID-19 vaccine. On the basis of prior studies and seroconversion data from the Tanzanian setting, we assumed an 88% seroconversion rate for the control group (Sinopharm) and expected a 90% seroconversion rate in the experimental group. A noninferiority margin of 20 percentage points was set, meaning that TANCoV-1.3.20 would be considered noninferior if its seroconversion rate was not more than 20% lower than that of Sinopharm. Using a 1-sided significance level (α) of .05, 80% power (1−β), and a 1:1 allocation ratio (experimental: control), the required total sample size was estimated at 50 participants per group. The study includes 3 study groups, with 25 participants per arm, resulting in a total planned sample size of 150 participants. This sample size provides sufficient power to establish noninferiority if the lower bound of the CI for the difference in seroconversion remains above the preset margin. The calculation assumes binomial proportions and follows standard methods for noninferiority designs in parallel trials [30].

### Randomization

Eligible participants will be randomized to the intervention arm or control arm via permuted block randomization with a block size of 6 stratified by site. This method ensures a balanced allocation of participants among the groups. Participants fulfilling the eligibility criteria will be randomized sequentially, and each participant will have a unique randomization code. A randomization schedule will be created by an independent statistician via permuted-block randomization of variable size.

Before enrollment, the study screening electronic case report form must be completed. When a participant is confirmed to be eligible and has consented to be enrolled, their details will be entered on the next available line of the enrollment register to ascertain the trial number assigned to that participant, which will be used on all trial documents. This number is unique and will not be used for any other participant.

### Blinding

Blinding will be performed for the investigators and participants. Participants receiving the IP through nasal drops will also be provided with a normal saline injection, which is intended to prevent unblinding. Those who receive the Sinopharm vaccine through intramuscular injection will receive normal saline nasal drops (placebo nasal drops), which are also intended to prevent unblinding. Unblinding will be discouraged during vaccination; however, if a trial clinician considers it necessary for a participant’s allocated vaccination to be unblinded, this should first be discussed with the principal investigators and other key investigators. If unblinding is deemed appropriate, the reason for doing so should be recorded. In the event that adverse vaccine reactions are considered possibly related to the study vaccine, the study vaccine will be discontinued for the affected participant.

### Study Sites

The clinical sites will be located at Mwananyamala Regional Referral Hospital in Dar es Salaam for the National Institute of Medical Research (NIMR) Muhimbili and the NIMR-Mbeya Medical Research Center in Mbeya, Tanzania.

For the Dar es Salaam site, all safety laboratory tests will be performed at the Muhimbili National Hospital Central Pathology Laboratory, and PBMC processing will be conducted at the National Public Health Laboratory. For the Mbeya site, laboratory tests will be carried out at the NIMR-Mbeya Medical Research Center safety laboratory. All samples for immunogenicity analysis will be analyzed at the NIMR-Mbeya Medical Research Center Immunology Laboratory.

### Inclusion and Exclusion Criteria

Inclusion criteria are (1) healthy individuals aged 18 to 45 years at screening and who are willing to provide written informed consent, (2) individuals whose BMI falls between 18.0 and 34.9 kg/m^2^, (3) willingness to undergo COVID-19 testing and negative antigen and antibody tests, (4) satisfactory completion of an assessment of understanding before enrollment, (5) resident in Dar es Salaam or Mbeya and willing to remain in the same region for the duration of the study, and (6) consistent use of effective contraception for individuals who can become pregnant and should have a negative pregnancy test at enrollment.

Exclusion criteria are (1) active tuberculosis or other systemic infectious processes elicited by a review of systems, physical examination, and laboratory testing; (2) history of immunodeficiency or chronic illness requiring continuous or frequent medical intervention; (3) HIV, hepatitis B, and/or hepatitis C infection; (4) received blood or blood products or immunoglobulin in the past 3 months; (5) hives or recurrent hives and severe eczema; (6) history of psychiatric, medical, and/or substance abuse problems during the past 6 months; (7) history of grand mal epilepsy or currently taking antiepileptic medications; (8) receiving immunosuppressive therapy; (9) have received experimental therapeutic agents, currently or within the last few months; (10) previously received COVID-19 candidate vaccines such as Janssen, Sputnik, SINOVAC, Sinopharm, Pfizer, and Moderna, or received any live attenuated vaccine within 90 days before enrollment; (11) history of severe local or general reactions to vaccination; (12) lactating mothers; and (13) individuals deemed unlikely to comply with protocol procedures as judged by the investigators.

### Study Procedures

#### Overview

Briefing sessions containing general information about the study, counseling, and prescreening procedures will be conducted at the trial site clinic and different venues in the community, including open spaces and police or prison facilities. All trial-related activities and vaccinations will take place at the clinical trial sites. Before the study procedures, participants will go through the consent process and will sign 2 copies of the informed consent form. One copy will be kept at the trial site, and the other copy will be provided to the study participant. TANCoV-1.3.20 vaccinations will be administered 4 weeks apart for individuals who will receive the booster dose, and the total follow-up duration will be 6 months. No further vaccinations will be administered in cases of consent withdrawal, confirmed pregnancy, or adverse drug reactions considered possibly related to the study vaccine.

#### Sample Collection

Blood, urine, saliva, and nasopharyngeal samples will be collected according to the visit schedule. These samples will be collected as per specific trial standard operating procedures.

#### Pregnancy Reporting and Follow-Up

Female participants will be required to use an effective contraceptive method starting 1 week before the first vaccination and continuing until 3 months after the last vaccination. A pregnancy test will be performed according to the study flow schedule. For participants who become pregnant before completing the vaccine series, no further vaccinations will be administered. A positive urine pregnancy test result will be communicated to the participant and the sponsor. The participant will be monitored for all the remaining scheduled visits according to the schedule of procedures for safety evaluation, as well as for maternal outcomes during pregnancy, labor, delivery, and postdelivery periods. The infant’s outcome will also be documented on the pregnancy outcome form.

#### Safety Assessment and Reporting

Safety assessment will be based on monitoring AEs, complications, and side effects, which will be collected throughout the study. Any AEs or SAEs encountered will be reported and categorized by the reviewing ethics committee and the Division of AIDS toxicity table for grading the severity of adult and pediatric adverse events.

Local and systemic assessments will be recorded starting 30 minutes after vaccination at the following intervals: 30 minutes as direct observation after vaccination at the clinic and days 1 to 7 at the clinic or home via the reactogenicity form and diary cards at the clinic and home, respectively. All other medical events, including laboratory safety assessments throughout the entire study period, will be reported on the AE form.

#### Immunogenicity Assessment

The processed samples (sera) will be analyzed to evaluate immunoglobulin G (IgG) and immunoglobulin M (IgM) titers using the WANTAI SARS-CoV-2 Ab enzyme-linked immunosorbent assay. The resulting antibody concentrations will be quantified, and the values will be expressed as GMTs to provide a reliable summary measure of the immune response while minimizing the effect of extreme values or outliers.

In addition to humoral responses, the cell-mediated immune response will be characterized to provide insights into T-cell activation and cytokine production following vaccination. This will include an interferon-γ (IFN-γ) enzyme-linked immunospot assay to quantify antigen-specific T-cell responses, alongside an intracellular cytokine staining assay performed on cryopreserved PBMCs. The intracellular cytokine staining assay allows detailed profiling of cytokines such as IFN-γ, interleukin-2 (IL-2), tumor necrosis factor-α (TNF-α), and other relevant markers, enabling the evaluation of T-cell subsets (cluster of differentiation 4 [CD4^+^] and cluster of differentiation 8 [CD8^+^]) involved in vaccine-induced immunity.

All immunology work and long-term sample storage, for at least 15 years, will be centralized at the NIMR-Mbeya Center.

### Data Management

#### Overall Data Management

All the data will be collected and managed electronically via secure REDCap (Research Electronic Data Capture; Vanderbilt University) software. The data will be handled confidentially, and no names or any other identifying information will be used during report writing, results dissemination, or publication.

The standard operating procedures will be followed in all laboratories to ensure the quality of the data. All results from the laboratory will be reviewed and signed by the laboratory manager for completeness and correctness before being entered into the electronic system. Clinical laboratory results will be entered into an electronic database by the clinician after review.

The location of the data management center is Dar es Salaam at the NIMR Muhimbili Center. Data from both sites will be centrally checked for inconsistencies and logical errors by site supervisors before being uploaded. Copies, including documentation detailing all the queries and changes, will be stored in a study-specific binder at the trial coordination site. The data generated from the mixed methods component will be managed at NIMR-Mbeya, where audio-recordings and transcripts will be kept in password-protected folders within the center’s server.

#### Data Analysis

The data will be analyzed using Stata (version 14; StataCorp LLC). Findings will be reported according to the CONSORT (Consolidated Standards of Reporting Trials) guidelines. Primary analyses will be based on the intention-to-treat population, and secondary analyses will be based on the per-protocol population.

The primary end point will be analyzed via a marginal Poisson regression model fitted using generalized estimating equations, with the logarithm of follow-up time included as an offset and the study arm as the predictor. The incidence rate ratio and its 95% CI will be derived from the Poisson regression model. Incidence rates will also be calculated as the number of incident cases divided by the person-time in years, with person-time calculated from randomization to (1) the study end at 6 months after the last participant enrollment and (2) death or the time last seen if lost to follow-up. In addition, absolute effects on the primary endpoint will be summarized using risk differences (events per 1000 person-years) and their 95% CIs, estimated from the model-based predicted rates in each arm.

In a secondary analysis of the primary end point, we will adjust the Poisson regression model for covariates, defined a priori (age and sex). Each protocol analysis will be performed and defined according to reported adherence to the intended allocation. Subgroup analysis of the primary end point will also be performed via the Poisson model on the prespecified subgroup variables (age and sex).

Other secondary outcomes will be analyzed using generalized linear models, depending on their distributions. The mean difference with its 95% CI will be derived for a continuous outcome, and the odds ratio with its 95% CI will be estimated for a binary outcome.

AEs will be summarized according to the number and percentage of individuals experiencing AEs.

The quantitative and qualitative data for the mixed methods component will be analyzed separately and integrated for interpretation. The interviewer-administered questionnaires will be entered into REDCap and analyzed using Stata, mainly through descriptive analysis. Demographic characteristics will be summarized via descriptive statistical methods, where continuous data will be summarized by the mean, SD, median, and IQR, and categorical values will be summarized by frequency and percentages. A mean score of general acceptability will be computed; however, each of the responses to the 7 constructs of the TFA will be analyzed based on the proportions of acceptance and nonacceptance.

Thematic analysis will be adopted as an analytic technique for qualitative data with the use of ATLAS software (version 8.4.26; ATLAS.ti Scientific Software Development GmbH). The analysis will also be guided by the TFA. This entails verbatim transcription of audio recordings and translation into English, as well as coding of transcripts where emergent and preconceived codes, on the basis of the TFA, are attached to the transcripts. Thereafter, a first draft of the codebook, containing a list of codes and their explanations, will be developed prior to coding based on the TFA constructs. Thereafter, the first 2 transcripts of participants from each of the 2 sites were coded independently by 4 social scientists (2 from each site). Discrepancies in coding will be resolved through a discussion among social scientists, and an agreement on the coding will be sought to further refine the codebook. Emergent codes arising from the transcripts will also be added to the codebook.

Upon completion of coding, codes are grouped into subcategories and categories on the basis of similarities that exist among a group of codes in terms of content or context. This process involves the development of subthemes and themes that reflect the underlying meanings attributed to the categories. Upon completion of separate analyses of quantitative and qualitative data, the results of each dataset are integrated using a weaving approach.

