#### Statistical Considerations and Analysis

##### Statistical Analysis

An interim review of the data will be performed by the independent data and safety monitoring committee. This will be done when at least 80% of the participants have been followed for at least the first 3 months. This is beyond the halfway stage to ensure that the safety estimate calculated at this time is statistically stable. Early stopping is considered if the significance level is *P*=.001 or lower (ie, if the Haybittle-Peto boundary is used).

The final analysis will be conducted once all study participants have received all their vaccinations, completed the final visit, or permanently withdrawn from the study. Analyses will be based on the principles of intention-to-treat and per protocol.

Baseline characteristics will be summarized by study groups using appropriate summary statistics. The study participant characteristics to be summarized will include demographic variables and baseline values relevant to safety and immunogenicity. The number and percentage of participants experiencing any AEs or SAEs will be summarized by severity and their relationship with the study treatment for each group. The calculation of incidence rates of AEs will include each participant only once, either according to the worst severity or the first reported event. Rates of the various AEs will be compared between the study groups via the Fisher exact test and will be summarized via exact binomial CIs. Safety, hematological, and clinical chemistry laboratory parameters will be summarized at the study visit according to the study group. Comparisons will be performed using 2-sample *t* tests or nonparametric equivalents as appropriate for the data.

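### Two primary safety endpoints are fixed-window proportions, but the stated primary analysis is a person-time rate model whose clock runs past each participant's follow-up

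*Protocol article*

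**What the plan says.** The Safety End Points section of the Protocol article lists three endpoints, all as proportions of participants:

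- Endpoint 1 is "the proportion of participants with local and systemic solicited AEs from days 1 to 7 after each intraperitoneal (IP) administration".
- Endpoint 2 covers grade 2 or higher unsolicited events, including laboratory parameters, "from the day of each IP administration through 28 days after IP administration".
- Endpoint 3 covers serious adverse events over the whole study.

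The Data Analysis section analyses the primary end point with a marginal Poisson model (generalized estimating equations) that has log follow-up time as offset and arm as predictor. It defines "person-time calculated from randomization to (1) the study end at 6 months after the last participant enrollment", or to death or the time last seen for those lost to follow-up. Absolute effects are called risk differences but are given in events per 1000 person-years.

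On follow-up, the Overview under Study Procedures says "the total follow-up duration will be 6 months". The Abstract gives 6 months of recruitment and 6 months of follow-up after vaccination.

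The Statistical Analysis section describes another treatment of adverse events: "Rates of the various AEs will be compared between the study groups via the Fisher exact test", with exact binomial intervals. It also says: "The calculation of incidence rates of AEs will include each participant only once". Nothing states how this ranks against the Poisson model.

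**The concern.** The analysis and the endpoints answer different questions. Endpoint 1 asks what share of participants react in the week after a dose. A rate model with a follow-up offset asks how many events occur per year of follow-up, and it takes expected events to be proportional to total time. A participant with 12 counted months would be expected to have twice the first-week reactions of one with 6, although both had the same window.

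The calendar end adds a second problem. Someone who completes the 6-month schedule has neither died nor been lost, so as written the clock runs on until 6 months after the last enrolment. Time in which no visit takes place can then enter the denominator.

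At stake are the absolute safety figures, which are what a phase 1/2a trial chiefly reports. They would depend on how fast the trial recruited and would carry the wrong label. With two unranked analyses of the same events, the choice of main result is also left open.

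**Working it through.** **The plan's own figure.** The article gives no adverse-event rate and no safety power, so no safety figure can be reproduced. Its one calculation concerns day-28 seroconversion. With 88% and 90%, a 20-point margin, one-sided 0.05 and 80% power, n = (1.645 + 0.842)² × (0.88×0.12 + 0.90×0.10) / (0.20 + 0.02)² ≈ 25 per arm. That reproduces the plan, but it has no bearing on this point.

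**Inputs.** Recruitment of 6 months and follow-up of 6 months (Abstract); clock to 6 months after the last enrolment (Data Analysis); windows of 7 and 28 days (Safety End Points). Uniform recruitment, the event risks below and counting each participant once are assumptions.

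**Counted against observed time.** The first participant contributes 6 + 6 = 12 months and the last contributes 6. Under uniform recruitment the mean is 6 + 6/2 = 9 months.

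- If 6 months are observed from randomization: 1 − 6/9 = 33% understatement of absolute rates.
- If the 6 months run from the day 28 visit, about 7 months are observed: 1 − 7/9 = 22%.
- For other recruitment patterns over the same 6 months, mean counted time lies between 6 and 12 months. With 6 months observed, the understatement lies between 0% and 1 − 6/12 = 50%.

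**Same data, different headline.** Rate per 1000 person-years = 1000 × risk / (counted months / 12).

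| Quantity on the endpoint's own scale | 6 months | 9 months | 12 months |
|---|---|---|---|
| 40% risk in 7 days | 800 | 533 | 400 |
| 20% against 10%: difference of 10 points | 200 | 133 | 100 |

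The proportions and the 10-point difference do not move; the person-year figures halve across the range.

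**Share of counted time inside the window.** Nine months is 273.9 days. A single 28-day window is 28/273.9 = 10.2% of it and a 7-day window is 2.6%. A rate over all counted time is therefore about 9.8 and 39 times lower than a rate over the window itself.

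**Does the calendar end unbalance the arms?** The Randomization section uses permuted blocks of 6 stratified by site. In 10,000 simulated trials (two sites, uniform 6-month recruitment, 1:1, equal 30% risk), the ratio of mean follow-up between arms averaged 1.00, with a 95% range of 0.983 to 1.017 for 150 participants and 0.956 to 1.046 for one group of 50. The rate ratio divided by the risk ratio had the same mean and ranges.

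**Window definitions side by side.**

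- Endpoint 1 expands IP as intraperitoneal, while Table 1 shows only nasal and intramuscular administration. The Blinding section uses IP for the nasal product; the title of Table 1 uses investigational product for every group. Which administrations open a window, and in which arms, is therefore unclear.
- Endpoint 1 starts on day 1, yet vaccination is on day 0 and the Safety Assessment section says "Local and systemic assessments will be recorded starting 30 minutes after vaccination". Endpoint 2 starts on the day of administration.
- In Table 1 all arms receive something on day 28: Sinopharm in the controls, TANCoV in arm 1B, saline in arms 2B and 3B.

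**The case against.** The strongest defence is that the right analysis is already in the document. Fisher exact tests, exact binomial intervals and numbers and percentages of participants with events are all planned, so the proportions will be reported. This stands in part: the fault is an unranked and mismatched primary analysis, not an absent one.

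Endpoint 3 runs throughout the study and is not a fixed window, so person-time is much less out of place there. That stands, and the point is limited to endpoints 1 and 2. The rule of counting each participant once sits beside the Fisher and binomial summaries and is not stated for the Poisson model, so the two cannot simply be combined into a further error.

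A reader might infer that the model compares the arms over unequal windows and so favours TANCoV. The documents do not support this. Block randomization by site balances calendar follow-up. The narrow reading, in which only TANCoV opens a window, is one of two, since the title of Table 1 covers every group and the reaction assessments follow vaccination without restriction by arm. Fewer reactions after one active dose than after two would largely be a real difference between regimens in Groups 2 and 3, and any figure for it would rest on per-dose risks that the article does not give.

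The intraperitoneal expansion is probably an abbreviation slip, and day 0 reactions are recorded in any case. Both still need correcting because they sit inside a primary endpoint definition.

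**Conclusion.** The point holds for safety endpoints 1 and 2. The stated primary model does not estimate them, its absolute contrast is a rate difference labelled as a risk difference, and its clock conflicts with a follow-up of about 6 months per participant. Absolute rates would be understated by about 22% to 33% relative to observed time, given uniform 6-month recruitment and 7 or 6 months actually observed; other recruitment patterns change the size. The relative comparison between randomized arms is little affected, and no bias between arms is claimed. That balance assumes concurrent enrolment and no differential loss to follow-up; the article states nothing to the contrary.

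**What to change.** 1. For endpoints 1 and 2, name the proportion analysis as primary: risk difference with an exact or score confidence interval, alongside the Fisher exact test already planned. Remove the Poisson offset model for these two endpoints.
2. Keep person-time at most for serious adverse events. End it at each participant's own last visit, death or loss to follow-up, and call the contrast a rate difference.
3. Replace the intraperitoneal wording with each vaccination visit (day 0 and day 28) in all arms, whatever was given.
4. Report the post-day-0 and post-day-28 windows separately, because Groups 2 and 3 set two-dose controls against one-dose TANCoV.
5. Reconcile the day 1 start of the solicited window with the 30-minute assessment on day 0.
6. Record the change with a date before unblinding, since Recruitment and Study Progress says statistical analyses are underway.

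The cost is a wording change to the protocol and analysis plan. It calls for no assessment beyond those the article already describes, although laboratory testing was still ongoing at the time of writing.

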## Methods

### Study Design and Settings

This is a phase 1/2a double-blinded, randomized controlled phase trial that aims to assess the safety, tolerability, and immunogenicity of the TANCoV-1.3.20 SARS-CoV-2 vaccine candidate among healthy participants in the Dar es Salaam and Mbeya regions of Tanzania. In Dar es Salaam, participants are recruited from the general population and communities such as the police and prison forces, while in Mbeya, participants are recruited from the general population.

For the social component, a convergent mixed methods study using separate and parallel administrations of semistructured in-depth interviews and interviewer-administered questionnaires is embedded in the trial. The design enables the generation of an in-depth understanding of aspects of the trial that promote participants’ acceptance of trial participation. The theoretical framework of acceptability (TFA) will be used to guide the assessment of acceptability. The TFA consists of 7 component constructs, namely, affective attitude, burden, ethicality, intervention coherence, opportunity costs, perceived effectiveness, and self-efficacy [29].

A list of all enrolled participants per site, including their demographics and scheduled visits, will be developed to aid in purposive sampling and the scheduling of appointments for informed consent and data collection during follow-up visits.

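### Randomization is stratified by site, but the primary safety model and its adjusted version leave site out, at a cost in precision and power if adverse event risk differs between sites

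*Protocol article*

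**What the plan says.** All references are to the Methods of the protocol article.

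- **Randomization** specifies "permuted block randomization with a block size of 6 stratified by site".
- **Data Analysis**, primary model: a marginal Poisson regression "with the logarithm of follow-up time included as an offset and the study arm as the predictor".
- **Data Analysis**, adjusted model: "we will adjust the Poisson regression model for covariates, defined a priori (age and sex". Subgroup analyses are likewise run "on the prespecified subgroup variables (age and sex".
- **Data Analysis**, secondary outcomes: "Other secondary outcomes will be analyzed using generalized linear models, depending on their distributions". No covariates are named.
- **Statistical Analysis**: "Rates of the various AEs will be compared between the study groups via the Fisher exact test". Laboratory parameters are compared by two-sample t tests or nonparametric equivalents. Neither comparison is described as stratified.
- **Study Design and Settings**: "In Dar es Salaam, participants are recruited from the general population and communities such as the police and prison forces". Mbeya recruits from the general population only.
- **Study Sites**: for Dar es Salaam, "all safety laboratory tests will be performed at the Muhimbili National Hospital Central Pathology Laboratory". Mbeya uses its own safety laboratory. Immunogenicity samples from both sites go to one laboratory in Mbeya.
- **Safety End Points**: the second end point counts unsolicited events of grade 2 or higher and includes safety laboratory parameters.

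**The concern.** When allocation is balanced within site, the estimated arm difference no longer varies with the site mix. An analysis that ignores site does not know this. It leaves between-site variation in the error term, so its standard error is larger than the randomization justifies.

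The article's own description makes site a candidate prognostic factor for safety, because the source populations differ in part and the laboratories differ. It gives no comparable reason for choosing age and sex over the design factor.

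What is at stake is sensitivity. Safety is the primary objective, and a test that runs below its nominal level is less able to show an excess of adverse events.

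**Working it through.** **1. The plan's own figure.** Sample Size Estimation assumes seroconversion of 88% and 90%, a margin of 20 points, one-sided alpha 0.05, 80% power and 1:1 allocation.

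- Distance to the margin: 0.90 − 0.88 + 0.20 = 0.22.
- Variance term: 0.88×0.12 + 0.90×0.10 = 0.1956.
- n per arm = (1.6449 + 0.8416)² × 0.1956 / 0.22² = 6.1827 × 0.1956 / 0.0484 = 24.99, rounded up to 25.
- This gives 50 per group and 150 over three groups, as stated. Power at 25 per arm is 80.0%.

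The calculation has no site term, so adding site to the analysis leaves the stated size unchanged.

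**2. How much variance site could explain for a binary event.** With equal site sizes and site risks p1 and p2, the share is ((p1 − p2)/2)² / [p̄(1 − p̄)]. The risks are assumptions.

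- 20%/40%: 0.01/0.21 = 4.8%
- 10%/50%: 0.04/0.21 = 19.0%
- 10%/70%: 0.09/0.24 = 37.5%

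**3. Effect on the test.** The simulation used 10,000 runs per setting and two sites of 75 (assumed). Blocks of 6, three per arm, were stratified by site, giving about 75 participants per arm with the dose groups pooled. The outcome was a binary adverse event. The arm-only log risk ratio was compared with a Mantel-Haenszel risk ratio stratified by site, which stands in for a log-link model with site. Both tests were two-sided at 0.05.

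| Site risks | Type I, arm-only | Type I, by site | Risk ratio | Power, arm-only | Power, by site | Difference |
|---|---|---|---|---|---|---|
| 30%/30% | 0.0440 | 0.0430 | 1.6 | 0.5964 | 0.5939 | −0.0025 |
| 20%/40% | 0.0428 | 0.0464 | 1.6 | 0.6138 | 0.6458 | +0.0320 |
| 10%/50% | 0.0223 | 0.0397 | 1.6 | 0.6270 | 0.7604 | +0.1334 |
| 10%/70% | 0.0123 | 0.0445 | 0.6 | 0.5501 | 0.6813 | +0.1312 |

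The Monte Carlo standard error of each power is at most √(0.25/10,000) = 0.005, so the first row shows no real difference. The arm-only test never exceeds 0.05. It becomes conservative as the site risks separate.

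**4. Continuous outcomes.** In a linear model, omitting site inflates the standard error by 1/√(1 − R²), where R² is the share of variance due to site. Assumed shares of 5%, 10% and 20% give 1.026, 1.054 and 1.118. This formula suits laboratory values and log titres; it does not carry over directly to the Poisson model.

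**The case against.** **The planned analysis is valid.** This stands. At worst it is conservative, and if the sites have equal risks, adjusting gains nothing. Losses above 10 points appeared only at 10%/50% and 10%/70%, which are wide gaps. Eligibility criteria and the grading table are common to both sites, standard operating procedures apply in all laboratories, and data are checked centrally. Site may therefore matter little, and nothing shows that it is the strongest prognostic factor.

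**Site imbalance.** A reader might infer that chance imbalance between sites could distort the laboratory comparison. The documents do not support this. With blocks of 6 at three per arm, the arms differ by at most 3 within a site. This relies on the allocation having been carried out as described. The article does not say whether the participants added to reach 169 were allocated within site.

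**Reach of the omission.** A reader might also infer that every analysis excludes site. That is a stated choice only for the Poisson model. The secondary generalized linear models name no covariates, and Immunogenicity Analysis lists its tests as examples and leaves its longitudinal models open. An unseen analysis plan may include site there.

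**Laboratory difference.** It bears on safety only, because immunogenicity assays are centralized. For titres, the case for site rests on the stratified design and the population difference.

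**The unseen analysis plan.** It could be said to settle the Poisson model too. This does not stand. The article declares the covariate list as fixed in advance, and site is not on it.

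**Conclusion.** The point holds as one of efficiency. The article randomizes within site and then fixes a primary safety model, and an adjusted version of it, without site. The consequence is conservative inference and lost power, without bias or inflated type I error.

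The size is undocumented because no site-specific risks are given. Under the assumed risks, the loss runs from nil when they are equal, through about 3 points at 20%/40%, to about 13 points at 10%/50%. These figures rest on equal site sizes, a binary event, dose groups pooled and stratified blocking working as described. Comparisons within a single dose group, at 25 per arm, were not simulated. The omission itself is certain from the text; how much it matters in this trial is not known.

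**What to change.** Before any unblinded comparison:

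- Add site as a fixed effect to the primary Poisson model and to the age- and sex-adjusted model. Keep the incidence rate ratio. Keep the model-based rate difference, with predicted rates averaged over the trial's site mix.
- Report the arm-only model as a sensitivity analysis.
- Compare continuous laboratory values and log titres with linear models that include arm and site.
- Include site in the secondary generalized linear models where event counts allow.
- For sparse outcomes such as serious adverse events, keep exact, unstratified results by arm.

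**Cost.** Site is known for every participant, so no new data are needed and the sample size does not change. There are two drawbacks. Models with few events may become unstable, hence the exact fallback. For binary outcomes reported as odds ratios, the site-adjusted estimate is conditional on site, so it targets a different quantity from the unadjusted one and need not have a smaller standard error. The report should say which is presented.
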